## Abstract

**Introduction:**

Patients with episodes of supraventricular tachycardia (SVT), a common heart arrhythmia, are often attended by ambulance services. International guidelines advocate treatment with the Valsalva manoeuvre (VM), but this simple physical treatment has a low success rate, with most patients requiring conveyance to hospital. The Valsalva Assist Device (VAD) is a simple device that might help practitioners and patients perform a more effective VM and reduce the need for patients to be taken to hospital.

**Methods and analysis:**

This stepped wedge cluster randomised controlled trial, conducted within a UK ambulance service, compares the current standard VM with a VAD-delivered VM in stable adult patients presenting to the ambulance service with SVT. The primary outcome is conveyance to hospital; secondary outcomes measures include cardioversion rates, duration of ambulance care and number of subsequent episodes of SVT requiring ambulance service care. We plan to recruit approximately 800 patients, to have 90% power to detect an absolute reduction in conveyance rate of 10% (from 90% to 80%) between the standard VM (control) and VAD-delivered VM (intervention). Such a reduction in conveyance would benefit patients, the ambulance service and receiving emergency departments. It is estimated potential savings would pay for devices for the entire ambulance trust within 7 months.

**Ethics and dissemination:**

The study has been approved by the Oxford Research Ethics Committee (reference 22/SC/0032). Dissemination will be through peer-reviewed journal publication, presentation at national and international conferences and by the Arrhythmia Alliance, a patient support charity.

**Trial registration number:**

ISRCTN16145266.

Strengths and limitations of this studyThe efficient, pragmatic design of the trial and use of routine data, enables delivery of the study during normal ambulance service care of patients with supraventricular tachycardia, as the device is brought into standard use.The study is designed to detect a difference in conveyance rate; a reliable outcome that is of importance to patients, the ambulance service and receiving hospitals.Although individual participant randomisation and blinding is not possible in this study, blinding of the trial statisticians will be maintained until the statistical analysis plan is finalised and signed off by the Trial Steering Committee.

## Introduction

Supraventricular tachycardias (SVT) are a group of common heart rhythm disorders causing episodes of fast heart rates. The incidence of SVT is estimated to be 35 episodes per 100 000 persons/year^1^ and attacks are unpleasant and disruptive to patients’ lives.^2^ SVT often occurs because of an additional electrical pathway in the heart, causing a ‘re-entrant tachycardia’.

Prehospital emergency services often attend patients with attacks of SVT. A regional Australian ambulance service recorded seeing 800 cases of SVT in a year^3^ with audit data suggesting a similar number of episodes in the South Western Ambulance Service NHS Foundation Trust (SWASFT), in the South West of England, UK. International ambulance treatment guidelines recommend initial treatment with the Valsalva manoeuvre (VM).^4 5^ This simple physical treatment involves an exhalation strain against resistance which causes a slowing of the heart (mediated by the vagal nerve) and can cardiovert an SVT back to normal sinus rhythm. Unfortunately, cardioversion rates in routine prehospital practice can be as low as 5% and most patients are conveyed to hospital with ongoing SVT.^6 7^

Results from our feasibility study suggested SWASFT ambulance clinicians treat around 500 of the SVT episodes they see each year, using a VM with approximately 90% of these patients being conveyed to hospital.^8^ This ambulance service has previously adopted the modified Valsalva manoeuvre (mVM) into its guidelines as the first-line treatment in stable patients with SVT. This guideline, in common with others, recommends that the VM strain is delivered by blowing into a 10 mL syringe^9^ followed by an internationally recommended^10^ postural modification which has shown to improve cardioversion rates.^11^ However, syringes are unreliable in generating the correct VM strain pressure^12^ and remembering the modified manoeuvre may be difficult for individual clinicians, who only occasionally see these patients.

A simple, easy to use Valsalva Assist Device (VAD) has been developed which provides the correct, recommended resistance (40 mm Hg) for the VM exhalation strain.^13^ A Conformité Européene (CE) marked VAD has been produced by Meditech Systems Limited (www.meditechsystems.co.uk), marketed as the ‘Valsa-Valve’ VAD (see figure 1). This VAD includes instructions for use on the device and it’s packaging, including information on the timings and the postural changes required for the mVM. If appropriate, these single-patient-use devices can also be left with the patient, for subsequent use should an attack recur. The VAD might improve the quality of the VM and increase the chances of cardioversion and non-conveyance compared with the standard approach using syringe delivered VMs. Reducing ambulance conveyance of patients to hospital, when appropriate and possible, is increasingly important to health services and patients.^14^

**Figure 1 F1:**
[figure not shown]
The ‘Valsa-Valve’ Valsalva Assist Device packaging and device details. CE, Conformité Européene; QTY, quantity; REF, reference number; RH, relative humidity; SWASFT, South Western Ambulance Service NHS Foundation Trust.

A definitive randomised controlled trial is needed to test whether the availability of a VAD to ambulance clinicians, when treating patients with SVT, affects the success of treatment and the need for conveyance to hospital, compared with current practice. A recent feasibility study and patient and public feedback have informed the nature and design of the definitive trial outlined in this protocol paper.

## Methods and analysis

### General study design and conduct

This study is an efficient, pragmatic, stepped wedge cluster randomised controlled trial to see if the routine availability of a VAD and its instructions (intervention), to treat adult patients presenting to SWASFT ambulance clinicians with SVT, can reduce the rate of hospital conveyance compared with standard practice (control). The stepped wedge design involves the allocation of ambulance service clusters across the whole service. These clusters all start as controls, providing current standard care, before being randomly assigned to using the VAD, as a new standard treatment, in defined groups and periods over the duration of the study (further details provided below). This study protocol is reported according to Standard Protocol Items: Recommendations for Interventional Trials reporting guidelines.^15^

### Study population and setting

Eligible patients presenting to SWASFT with suspected SVT and who are treated with a VM by an SWASFT ambulance clinician, will be included. The study will be conducted entirely within SWASFT, UK. This ambulance service uses a searchable electronic patient care record (ePCR) as standard when attending patients. This was shown to be a reliable and easily searchable data source in our feasibility study. SWASFT also has an established clinical guideline advocating the use of an mVM and non-conveyance of successfully treated SVT patients.

The study aims to include all adult patients aged 18 years and over for whom there is a record of a VM delivered by an ambulance clinician, working out of a participating ambulance station, for presumed SVT.

Patients who subsequently withdraw consent for use of their data or have an existing general opt-out for use of routine National Health Service (NHS) data for research will be excluded from the trial. Data from patients who are prisoners at the time of treatment, patients with permanent lack of capacity as recorded by the treating clinician and patients solely treated by an SWASFT member of staff outside of the included ambulance station clusters (eg, air ambulance, Hazardous Area Response Team, British Association for Immediate Care doctor) will also be excluded. Data from patients previously included in the study will be excluded from the primary outcome analysis but will be used in analyses of some secondary outcomes. A summary table of the trial eligibility criteria is shown in table 1.

**Table 1 T1:** Trial inclusion and exclusion criteria

Inclusion criteria	Adult patients (age 18 years or over). Record of a Valsalva manoeuvre for presumed SVT having been delivered by an ambulance clinician assigned to a participating ambulance station cluster.
Exclusion criteria	Subsequent withdrawal of patient consent to use their data. Existing opt-out for use of NHS data for research. Data from patients who are prisoners at the time of treatment. Patients with permanent lack of capacity as recorded by the treating clinician. Patients solely treated by an SWASFT resource not from one of the included ambulance station clusters, for example, air ambulance, Hazardous Area Response Team, Tiverton Minor Injuries Unit, British Association for Immediate Care doctor. Data from patients previously included in the study will be excluded from the primary outcome analysis but will be used in analyses of some secondary outcomes.

NHS, National Health Service; SVT, supraventricular tachycardia; SWASFT, South Western Ambulance Service NHS Foundation Trust.

### Study procedures

Potential study participants will undergo standard clinical assessment by ambulance clinicians. For suspected SVT this typically includes medical history, recording of routine initial observations of pulse, blood pressure, respiratory rate, oxygen saturation and the recording of a 12-lead ECG. Routinely collected clinical data are entered into the ePCR system and so are available for subsequent trial data extraction for eligible participants.

The screening of eligibility for VM treatment, the conduct of the VM and all other aspects of clinical care will be entirely governed by SWASFT clinical guidelines, interpreted and followed at the discretion of the treating clinician. On commencement of the intervention phase of the trial, SWASFT clinical guidelines will be updated to include the use of the VAD, where available as part of standard care.

### Trial treatment

The stocking of ambulances with the VAD (and thus the allocation of interventions) will be determined by the randomisation schedule as described below. This will ensure that a VAD is available for use by the treating clinician according to the randomisation schedule. The use of devices will thereafter be at the discretion of the treating clinician but encouraged through trial training and publicity; device use will be recorded and used as a measure of device acceptability.

Post-treatment assessment usually includes the recording of a further 12-lead ECG to determine whether normal sinus rhythm has been restored. However, this is not universal and often omitted if there has been no clear change in the heart rate and rhythm. SWASFT guidelines allow for non-conveyance in stable, well patients who have cardioverted, have normal observations and remain in sinus rhythm after 20 min of observation. In this case, patients are advised to seek further follow-up with their general practitioner. Patients will also be given the device (syringe or VAD) they used to perform the VM to take away, with written instructions, in case of recurrent SVT attacks.

### Consent

All patients will be given a participant information leaflet (PIL), specific to the stage of the trial, at a convenient time after treatment, at the discretion of the treating ambulance clinician. The front of the PIL will clearly state that the information can be read when the patient is ready and feels well enough. The PIL contains an explanation of SVT, the nature of the trial and how to opt out, should they not want their data to be used. Ambulance clinicians will be asked to record in the ePCR, confirmation that the PIL was given to the patient or a carer. As part of the screening and data entry process, the Lead Research Paramedic will confirm whether a PIL was given by checking the ePCR and, if not recorded, will contact the treating paramedic to confirm. If there is no evidence that a PIL was given at the time of treatment, the Lead Research Paramedic will post a PIL to the patient.

For patients with temporary lack of capacity (eg, due to their condition or associated illness) the PIL will be given to the next of kin or carer, if available, to explain and share with the patient when they are well enough. Patients with permanent severe lack of capacity, as determined by the treating ambulance clinician, will not be included. PIL translations will be sent to non-English speakers by SWASFT research staff where possible.

The PIL gives details of how patients can opt out of their routine data being used in the trial. This can be through immediate verbal opt-out (to the treating ambulance clinician) or retrospectively by telephone, post or email. Immediate verbal opt-outs will be recorded on the ePCR and screening of cases for inclusion in the trial data set will include a full search for opt-outs in the ePCR or received by any other means. An opt-out received at any time during the trial will render the patient ineligible, and their clinical data for their initial and subsequent episodes will not be included in the study. Safety follow-up data, already recorded up to the point of withdrawal, will be kept.

In the UK, patients also have the option to nationally opt out of having any of their routine digital NHS data used for research. The national rate of this type of opt-out currently stands at around 5%. After taking advice from the regional research ethics committee and our public and patient advisory group, we have elected to exclude all patients with a national data opt out unless the patient advises that they want to be included in the study (details of how to do this are included in the PIL).

In the absence of (i) the patient having a national opt-out and (ii) the research team receiving any individual opt-out, inferred consent for routine data use will be assumed. There is a precedent for this approach to collecting routine data for emergency medicine research and it is considered to constitute active recruitment as stated in the National Institute for Health and Care Research (NIHR) Clinical Research Network (CRN) recruitment policy document.^16^

Individual trial participation will last from the start of the SVT ambulance service care episode until 3 months after this time to enable the collection of further ambulance service use data as part of the planned recurrent SVT and safety follow-up period.

### Health-related quality of life data

The PIL also includes an invitation to an optional questionnaire to collect (non-routine) data on the effects of the participant’s condition and ambulance service treatment on their health-related quality of life. The invitation includes a web link (with a QR code) to this part of the study, printed on the PIL. Those who choose to participate will be given further information and asked for consent if they follow this link. Once they have given consent, they will be asked to complete the EQ-5D-5L (EuroQol health related quality of life instrument) questionnaire online, ideally within a week of the patient feeling well enough to complete the form; this will also be explained in the PIL. Participants who consent to this study component will be contacted digitally and reinvited to complete the EQ-5D-5L, 3 months after the SVT ambulance service care episode. Data from completed forms will be linked with the study database entry for the index presentation. Paper or emailed copies of the EQ-5D-5L will be sent to participants if requested, as outlined in the PIL. Paper or online EQ-5D-5L will be used under licence.

### Formation of ambulance station clusters and randomisation

Ambulance station clusters will be formed from the 93 SWASFT ambulance stations in existence at the time of study set-up. Recent historical data on activity and general conveyance rates for all stations were collected to inform the formation of trial clusters and sample size calculations. After merging very small and closely located stations, while maintaining the largest possible number of similar sized clusters, 80 (mostly single station) ambulance station clusters were identified. Clinicians working from these stations use equipment bags strictly belonging to and stocked by that station.

The stepped wedge trial design is comprised of five stages, with each stage lasting 4 months. In the first stage, none of the station clusters will have access to the VAD and patients will be treated as per standard practice. The clusters will then be randomly allocated, by computer-generated sequences (stratified by location and balanced on cluster size), to include VADs with their equipment bags, in one of the four remaining stages, so that 20 clusters and their clinicians receive access to the VAD for the first time at each stage. Randomisation will be performed by an independent statistician otherwise unconnected with the trial.

Once the VAD has been introduced, the cluster will retain the use of devices for the remainder of the study so that by the fifth stage, all 80 clusters and their clinicians will have access to the VAD (see figure 2). Devices will be added to a clearly marked ‘Valsalva pouch’ attached to the standard equipment bag. These bags are checked and restocked daily and carried by all treating ambulances. All station clusters randomised to VAD use will initiate availability of the VAD on the same day, coordinated by SWASFT supply logistics and the local ambulance station ‘champions’ (listed as trial collaborators). These processes will be overseen by the Clinical Trials Unit to ensure protocol compliance as far as possible. Ambulance stations will be notified of activation with sufficient time to enable Valsalva pouches to be changed and all station clinicians to be notified. No other individuals outside the Lead Research Paramedic, logistics supply chain and the station clinicians will be made aware of the randomisation.

**Figure 2 F2:**
[figure not shown]
Scheme for the randomised stepped wedge introduction of the Valsalva Assist Device to the ambulance service.

The timing and duration of cluster activation will only be changed in response to unexpected (high or low) rates of participant recruitment and only by agreement of the Trial Management Group (TMG), Trial Steering Committee (TSC) and sponsor.

To maintain blinding of research staff, all station clusters will be given a unique code that will be used in the clinical report form (CRF). A specific protocol (see below) will also be used to accurately identify the treating cluster (and hence treatment allocation) at the time of patient participation.

### EVADE cluster identification protocol

The process for determining the origin of the attending ambulance (and hence the equipment bag available to the treating clinician and allocation) will be according to a strict protocol. This will ascribe the correct cluster assignment while maintaining researcher blinding. Once the cluster is identified, it will only be identified in the CRF by its unique trial ID number. The hierarchy for determining cluster identification (and therefore, the intention-to-treat treatment allocation) is summarised below. Where more than one crew has attended a participant, it will be the first treating crew (as long as they are from a participating station) that will be used to identify the station allocation. The actual treatment used (as recorded in the ePCR) will also be recorded to inform any per-protocol analysis.

The treating cluster will be identified by:

Determining in the ePCR, which station the standard equipment bag originated from.If the station/cluster cannot be confirmed in this way, the lead clinicians involved will be emailed (likely one of two possible stations).Failing that, station champions will be emailed to request local inspection of drugs books (again likely to be one of two possible stations).Finally, if the cluster cannot be identified through the above steps, support will be requested from the SWASFT Clinical Information and Records Office to access the computer assisted dispatch system to provide geographical location coordinates but not address to identify the most likely treating cluster. If required, the Global Rostering System may also be used to identify which ambulance stations clinicians were working from.

### Independent ECG review

To estimate diagnostic appropriateness, a review of available pre-VM ECGs from the ePCR will be undertaken by an independent assessor (consultant electrophysiologist) blind to treatment allocation. Traces with severe interference, preventing interpretation, will be excluded. All other traces will be classified as eligible for VM (eg, re-entrant SVT, undetermined SVT) or ineligible VM (eg, atrial fibrillation, atrial flutter, sinus tachycardia). In practice, for normal treating clinicians, it can sometimes be challenging to distinguish between some of these ECG rhythms and VM is appropriate and safe if clinicians believe, on the evidence available, that the patient has an eligible SVT.

### Safety monitoring

The VM is a very safe, standard intervention with no evidence of harm in previous large studies. There is no reason to believe the trial intervention will pose any additional risks or significant delay in the patient’s treatment. However, any problems or adverse events during any VM or in the care of trial patients will be recorded, closely monitored and reviewed by the TMG and TSC. Adverse events will be recorded by the prehospital clinician in the ‘Datix’ reporting system used by SWASFT, screened for during data entry and brought to the attention of the Lead Research Paramedic for further consideration. Further ambulance attendances over the following 3 months from the index attendance will also be reviewed and monitored as part of trial safety monitoring.

An adverse event is classified as a serious adverse event (SAE) if it results in death, is life-threatening, requires hospitalisation or prolongation of existing hospitalisation, results in persistent or significant disability or incapacity, causes a congenital anomaly or is considered by the investigator to be an important medical event. Admission to hospital required for the presenting SVT or associated condition will not be considered an SAE in this trial. However, the reason for admission will be recorded and any admissions that are not clearly related to the participant’s presenting condition will be reviewed to assess whether they should be recorded as an SAE.

Any SAE recorded through the Datix system will also be brought to the attention of the chief investigator, who will assess it for possible causality linked to the trial in any way. All SAEs will be reported to the sponsor and reviewed by the TSC. The trial may be stopped if any indication of harm is found.

### Outcome measures

#### Primary outcome

The primary outcome of the study will be the percentage of participants treated with a VM by the ambulance service, who are conveyed to hospital, as determined by the SWASFT ePCR. This includes a mandatory record of the participant’s final destination for each care episode. The reasons for conveyance will also be recorded.

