#### Progress (RAG) criteria

The stepped wedge design is predicated on reliably recruiting the number of participants specified by the sample size calculation at each stage of the trial. Monthly recruitment will be monitored closely by the TMG and regularly reported to the TSC. Recruitment below target (amber or red criteria) will trigger a remedial plan by the TMG with promotion of the SVT guideline and trial awareness and feedback on missed cases (where a VM was indicated but not undertaken) in addition to the planned promotion of the trial (newsletters, posters, etc) and NIHR CRN support. Financial constraints would preclude significant trial prolongation and if, despite these measures, trial recruitment was less than 80% of our overall target for the first 4 months of the study, we propose discussion with the TMG, TSC and funder to consider trial termination or agreed modification.

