## Conclusions

The EVADE SVT trial will seek to determine whether the routine availability of a simple device (VAD) and its instructions to assist the ambulance service delivery of the VM to treat SVT reduces the proportion of patients with SVT that are conveyed to hospital. This trial protocol has been developed to deliver this trial within one large UK ambulance service during routine care. It is designed to detect a meaningful change in conveyance rate that would be of benefit to patients and emergency services and be relevant to other ambulance and emergency services around the world.

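### Trial entry and the primary denominator depend on a VM given after allocation by unblinded clinicians, so who is counted could change when a cluster receives the VAD

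*Protocol article*

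**What the plan says.** Table 1 (Study population and setting) admits adults with a "Record of a Valsalva manoeuvre for presumed SVT having been delivered by an ambulance clinician assigned to a participating ambulance station cluster". Under Primary outcome, the measure is "the percentage of participants treated with a VM by the ambulance service, who are conveyed to hospital". Data analysis assigns each patient to intervention or control by the cluster's status when the VM was given.

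Under Study procedures, screening for a VM and its conduct follow the service guideline, "interpreted and followed at the discretion of the treating clinician". The same section says that when the intervention phase begins "SWASFT clinical guidelines will be updated to include the use of the VAD, where available as part of standard care". The strengths and limitations box says that blinding is not possible. The section on cluster formation and randomisation says that station clinicians are told of activation in advance.

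Two sections bear on how many SVT attendances receive a VM:

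- The Introduction says that audit data suggest a yearly number of SVT episodes similar to the 800 of an Australian service, and that "SWASFT ambulance clinicians treat around 500 of the SVT episodes they see each year" with a VM.
- Determination of sample size reports 63 eligible VM patients in one month (95% CI 50 to 77), found with the proposed trial methods.

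The Conclusions state the aim as learning whether VAD availability "reduces the proportion of patients with SVT that are conveyed to hospital".

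**The concern.** In a stepped wedge trial, randomisation protects the comparison of everyone who would be counted whatever the cluster's status. Here a patient is counted only if a clinician who knows that status decides to give a VM. If having the VAD makes clinicians readier to try a VM, or to try it in different patients, the intervention and control groups stop being comparable. A difference in conveyance could then arise partly from who entered.

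The planned methods do not remove this:

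- Intention to treat by cluster status deals with non-use of the device, not with entry that depends on allocation.
- The fixed stage effect removes drift common to all clusters in a stage. A change that starts when a cluster gets the VAD follows the intervention indicator and is absorbed into the intervention effect.
- The blinded ECG review covers only patients who had a VM and an interpretable trace, and Data analysis does not link it to the primary model.
- The comparison of patient characteristics may show an imbalance, but it cannot show who was not given a VM.

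**Working it through.** **Plan's own figure.** The Hussey and Hughes variance was computed with 80 clusters, 5 stages, 20 clusters crossing per step, 2 patients per cluster-stage, total variance 0.10 × 0.90 = 0.09 and ICC 0.01.

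- Between-cluster variance τ² = 0.01 × 0.09 = 0.0009. Variance of a cluster-stage mean s² = (0.09 − 0.0009)/2 = 0.04455.
- Design sums: U = 200, W = 12,000, V = 600.
- Var = 80 × 0.04455 × (0.04455 + 5 × 0.0009) / [(80 × 200 − 12,000) × 0.04455 + (200² + 80 × 5 × 200 − 5 × 12,000 − 80 × 600) × 0.0009] = 0.1748/189.0 = 0.000925, so SE = 0.0304.
- Power = Φ(0.10/0.0304 − 1.96) ≈ 90.8%.

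The stated 800 for 90% power is reproduced. The SE serves below only as a yardstick.

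**Share of SVT attendances given a VM.**

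- Introduction: 500/800 = 62.5%. The VM group could grow by 300/500 = 60%.
- Pre-trial month: 63 × 12 = 756 a year (interval 50 × 12 = 600 to 77 × 12 = 924). 756/800 = 94.5%. The VM group could grow by 44/756 = 5.8%, and the interval includes no growth at all.

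These figures do not agree. The 800 is only a statement of similarity, and the 63 is a single month.

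**Size of a shift.** Let f be the growth of the VM group after rollout, as a fraction of the existing group, and q the non-conveyance rate of the added patients. Baseline non-conveyance is 10%. With no device effect, apparent non-conveyance = (0.10 + f × q)/(1 + f). Neither f nor q is in the documents. The value 0.058 uses all the room left by the 756 count. The value 0.20 is a chosen illustration, a third of the room left by the 500/800 ratio.

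| f | q | Apparent non-conveyance | Spurious gain |
|---|---|---|---|
| 0.058 | 0.30 | 0.1174/1.058 = 11.1% | +1.1 points |
| 0.20 | 0.30 | 0.16/1.20 = 13.3% | +3.3 points |
| either | 0.10 | 10.0% | 0 |

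With SE 0.0304, the chance of a two-sided p below 0.05 without any device effect is about 6.5% in the first row and about 20% in the second, against a nominal 5%.

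**Other direction.** If the device truly raises non-conveyance to 20% and every added patient is conveyed, the VAD rate is 0.20/(1 + f). At f = 0.058 it is 18.9%, a gain of 8.9 points. At f = 0.20 it is 16.7%, a gain of 6.7 points instead of 10.

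**The case against.** The strongest reply is that little in the protocol points to a rise in VM use tied to VAD status. The VM is already the first-line guideline treatment in the control condition. Under Trial treatment, "The use of devices will thereafter be at the discretion of the treating clinician but encouraged through trial training and publicity" concerns which device is used, not whether a VM is tried. The remedial measure "feedback on missed cases (where a VM was indicated but not undertaken" is triggered by low recruitment and is not tied to VAD status. Its formal check comes after 4 months, when no cluster has the device, and the stage effect would absorb a service-wide push. All of this stands. A reader might infer that the plan itself drives VM use up in VAD clusters, but these passages do not show that.

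A reader might also take 500 of 800 to mean that over a third of SVT patients go without a VM. The pre-trial month contradicts this, so the documents do not establish an untreated pool of that size.

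The aim in the Conclusions can fairly be read as shorthand for the VM-treated population defined elsewhere. Some safeguards deserve credit: ECG reading blind to allocation, comparison of patient characteristics, and recorded reasons for conveyance.

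Supportive analyses are commonly left to an analysis plan. However, this document fixes eligibility and the denominator. An analysis plan cannot analyse attendances without a VM unless someone extracts them.

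**Conclusion.** The point holds as a risk built into the design, not as a demonstrated bias. Entry follows allocation, depends on clinicians who know it, and is not protected by the stage effect or by intention to treat. The documents settle neither size nor direction. Under the assumed 30% non-conveyance among added patients and no device effect, the spurious gain runs from about 1 point (6% more VM patients) to 3.3 points (20% more), that is, from a tenth to a third of the 10-point target. It is zero if added patients match the baseline, and a true effect would be diluted if they are mostly conveyed. It would be going too far to say that the trial will favour the VAD. The change is worth making because it is cheap and shows whether entry differed by VAD status.

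**What to change.** Keep the primary outcome and add the following before database lock:

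1. Extract from the ePCR, as aggregate counts by cluster and stage, all adult presumed-SVT attendances: total, given a VM, conveyed.
2. Pre-specify the VM rate by VAD status, in the same stage-adjusted model with a random cluster effect.
3. Pre-specify conveyance among all presumed-SVT attendances as a supportive analysis.
4. Repeat the primary analysis in patients whose pre-VM ECG the blinded assessor already classifies as eligible.
5. State in advance that the conclusion will be worded for VM-treated patients if VM use differs by VAD status or the analyses disagree.

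The cost is one aggregate query per stage and a few further models. The estimate in step 3 is diluted by patients who get no VM. The presumed-SVT label is itself recorded by unblinded clinicians, so the wider denominator can shift too: it is a check, not a cure. Step 4 loses patients without an interpretable trace and still covers only VM recipients, so it guards against drift into ineligible rhythms and nothing more.
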